
**Fig. 1 Fig1:**
[figure not shown]
Participant flow chart

### Trial design and blinding

The trial is a randomised controlled superiority trial with two parallel arms using a 1:1 allocation ratio. Participants will not be blind to their group allocation. Follow-up interviews will be conducted by clinicians independent of the study and therefore blind to group allocation.

### Randomisation

Accepted participants will be randomised based on an allocation sequence generated by an independent person not involved in the study via a true randomisation process (www.random.org). Numbers corresponding to treatment group (1) or the waitlist control group (2) will be placed in sealed opaque envelopes bearing the sequential order number to ensure participant allocation based on the pre-determined randomisation sequence. A member of the research team will open the envelope after the diagnostic interview.

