**Methods/Design:**

Patients with PTSD will be recruited via the research arm of a not-for-profit clinical and research unit in Australia and randomised to a treatment group or waitlist control group. The minimum sample size for each group (alpha 0.05, power 0.80 for a *g* of 0.47) was identified as 72, but 10 % more will be recruited to hedge against expected attrition. PTSD diagnosis will be determined using the PTSD module from the Mini International Neuropsychiatric Interview version 5.0.0. The PTSD Checklist – Civilian version (PCL-C) will be used to measure PTSD symptoms (the primary outcome measure), with the Intolerance of Uncertainty Scale 12-item version (IUS-12) and the Emotion Regulation Questionnaire (ERQ) used to measure intolerance of uncertainty and emotion regulation, respectively. The PCL-C will be administered to the treatment group before each lesson of the PTSD program and at 3-month follow-up. The IUS-12 and ERQ will be administered before lessons 1 and 4, at post-treatment and at 3-month follow-up. The waitlist control group will complete these measures at week 1, week 5 and week 11 of the waitlist period. PTSD program efficacy will be determined using intent-to-treat mixed models. Maintenance of gains will be assessed at 3-month follow-up. Mediation analyses using PROCESS will be used to examine the association between change in PTSD symptoms over treatment and change in each of IU and emotion regulation ability in separate analyses.

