### Primary outcome measures

Administration time points for all instruments are contained in Table 1.

**Table 1 Tab1:** Administration time points for questionnaires used in the RCT

	Administration time point				
Measure	Pre-treatment	Before each lesson	Mid -treatment^d^	Post-treatment^e^	3-month follow-up^f^
LEC^a^	♦				
DES	♦				
MINI	♦				♦
PCL-C^b^	♦	♦	♦	♦	♦
BDI-II^c^	♦		♦	♦	♦
PHQ-9	♦		♦	♦	♦
K10	♦	♦	♦	♦	♦
GAD-7	♦		♦	♦	♦
CEQ	♦			♦	
IUS-12	♦		♦	♦	♦
ERQ	♦		♦	♦	♦
SUDOR	♦		♦	♦	♦
SAPAS	♦				

*LEC* Life Events Checklist, *DES* Dissociative Experiences Scale, *MINI* Mini International Psychiatric Interview, *PCL-C* PTSD Checklist **–** Civilian version, *BDI-II* Beck Depression Inventory – Second Edition, *PHQ-9* Patient Health Questionnaire 9-item version, *K10* Kessler Psychological Distress Scale 10-item version, *GAD-7* Generalised Anxiety Disorder 7-Item Scale, *CEQ* - Credibility and Expectancy/Satisfaction Questionnaire, *IUS-12* Intolerance of Uncertainty Scale 12-item version, *ERQ* Emotion Regulation Questionnaire, *SUDOR* Service Utilisation and Days Out of Role Questionnaire, *SAPAS* Standardised Assessment of Personality - Abbreviated Scale

^a^Refers to both LEC-IV and part 2 of LEC-5

^b^Includes items 10, 11, and 16 from PCL-5

^c^Item 9 only

^d^Waitlist control group completes these measures at week 5 of the waitlist period

^e^Waitlist control group completes these measures at week 11 of the waitlist period

^f^Treatment group only

**Posttraumatic stress disorder Checklist – Civilian version** (PCL-C) [40]. The PCL-C is a 17-item self-report questionnaire providing a continuous measure of PTSD symptomatology, conforming to Diagnostic and Statistical Manual of Mental Disorders, Fourth Edition (DSM-IV) diagnostic criteria. Each item reflects a PTSD symptom and is rated on a 5-point scale for distress (1 = “Not at all”; 5 = “Extremely”). Items 10, 11 and 16 from the PCL-5 [41] will also be administered, which assess new diagnostic criteria for PTSD in the fifth edition of the DSM [DSM-5 1]. This approach was adopted in favour of sole use of the PCL-5, which had not been validated at the time of trial design. This will enable examination of change in the new PTSD symptoms in DSM-5.

**PTSD diagnostic status**. Change in PTSD diagnostic status will be indexed using the MINI PTSD module. The MINI has sound reliability and validity psychometrics [39].

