### Participant monitoring

The Clinical Trials Manager of CRUfAD and a member of the research team will oversee participant monitoring. Symptom severity of the target disorder and general distress levels are measured before, during, and immediately upon completing the PTSD program based on empirically validated standardised internet-delivered symptom measures. Participants will be sent automated emails at the completion of each lesson to encourage skills practice. Patient queries throughout the program are primarily addressed by email contact from the clinician (AA) or the Clinical Trials Manager (JS). If clinically indicated, or if a patient’s K10 and/or PHQ9 or PCL-C scores deteriorate, the clinician makes telephone contact. If a participant misses a lesson, a member of the research team will send an email reminder (via the Virtual Clinic system) or will make telephone contact to remind the participant to complete the lesson.

The treatment group will be required to complete the iCBT program within 10 weeks to remain in the trial. Adherence is monitored throughout the program. Once enrolled, a participant can elect to discontinue at any time. A participant may be withdrawn from the trial (typically meaning course access will be closed) for the following reasons: lack of computer and internet access; change in prescribed medication for anxiety or depression; change in medication status of exclusion medications; suicidality or clinical risk; failure to complete baseline questionnaires; failure to commence the PTSD program. Lack of adherence throughout the iCBT program is not a specified reason for participant withdrawal, although a participant may withdraw voluntarily. Those in the waitlist control group will be required to complete questionnaires at weeks 1, 5 and 11 of the waitlist period to remain in the RCT. The waitlist control group will have access to the iCBT program immediately at the conclusion of the waitlist period. All reasons for withdrawal status will be documented.

To promote participant retention, participants are reminded that data collection is an important aspect of research and enables the research team to track their progress and to evaluate the program. Any adverse events will be reported to the Director of CRUfAD (GA) and to the Human Research Ethics Committee (HREC) of St Vincent’s Hospital, the responsible body for initiating a clinical trial audit.

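### Allocation is opened after the interview without requiring the baseline PCL-C, IUS-12 and ERQ first, and the rules for removing randomised participants differ by arm despite an intent-to-treat analysis

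*Protocol article*

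**What the plan says.** **Allocation.** Under Randomisation, "Accepted participants will be randomised based on an allocation sequence generated by an independent person not involved in the study", and "A member of the research team will open the envelope after the diagnostic interview". The interview is the only event to which opening the envelope is tied. Trial design and blinding adds: "Participants will not be blind to their group allocation".

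**First assessments.** The Abstract (Methods/Design) gives the schedule separately by arm. For the waitlist: "The waitlist control group will complete these measures at week 1, week 5 and week 11 of the waitlist period". For iCBT: "The PCL-C will be administered to the treatment group before each lesson of the PTSD program and at 3-month follow-up", and "The IUS-12 and ERQ will be administered before lessons 1 and 4, at post-treatment and at 3-month follow-up". The primary outcome is self-reported: "The PCL-C is a 17-item self-report questionnaire providing a continuous measure of PTSD symptomatology" (Primary outcome measures). Table 1 in that section also has a Pre-treatment column, marked for all three instruments.

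**Removal.** Participant monitoring lists, among the reasons a participant may be withdrawn, "failure to complete baseline questionnaires; failure to commence the PTSD program". It explains that withdrawal typically means course access is closed. The same section makes completion of the week 1, 5 and 11 questionnaires a condition for waitlist participants to remain in the trial.

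**Analysis.** Statistical methods specifies intent-to-treat mixed models fitted by REML, with significant effects followed by pre-to-post contrasts.

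**The concern.** A baseline used as the anchor for change should be recorded before anyone can know the allocation. If a person already knows that they must wait, or that they are about to start, a self-report scale can move for reasons unrelated to treatment. That movement then enters every pre-to-post comparison between arms.

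The order also decides who can drop out of the comparison. When baseline follows allocation, people who do not complete it have already been randomised, and removing them breaks the randomised groups. Failure to start the program can occur only in the iCBT arm during the comparison period, whereas the week 1, 5 and 11 condition applies only to the waitlist. The planned missing-at-random check compares drop-outs with the rest on baseline measures, so it cannot use the PCL-C, IUS-12 or ERQ of people who never completed them.

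**Working it through.** **1. The plan's own figure.** Inputs from Statistical methods: g = 0.47, alpha 0.05 (taken as two-sided), power 0.80.

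n per arm = 2(z₀.₉₇₅ + z₀.₈₀)² / g² = 2(1.960 + 0.842)² / 0.47² = 71.06, rounded up to 72. The t-test version gives 72.04. A one-sided test gives 56 and does not match. Adding 10% gives 72 × 1.1 = 79.2, or 80 per arm. The stated 72 reproduces, and nothing in this point changes it.

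**2. The order of events.**

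| Step | Where | Before or after the envelope |
|---|---|---|
| Online screening on symptoms and demographics | Participants and recruitment | Before; not named as the trial baseline |
| DES and PHQ-9 item 9 (exclusion criteria) | Participants and recruitment | Before |
| MINI interview | Participants and recruitment | Before |
| Waitlist first PCL-C, IUS-12, ERQ | Abstract; Participant monitoring | After: week 1 of a waitlist period cannot precede assignment to the waitlist |
| iCBT first PCL-C, IUS-12, ERQ | Abstract; Table 1 | Probably after: before lesson 1, but Table 1 lists Pre-treatment as a separate column |

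No sentence says that the PCL-C, IUS-12 and ERQ are completed before the envelope is opened.

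**3. Effect of a shifted baseline (assumed size).** The contrast is (post − pre) in iCBT minus (post − pre) in waitlist. If one arm's baseline moves by δ and its post-treatment score does not, the contrast moves by δ.

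- δ = 0.1 SD: 0.1 / 0.47 = 21% of the planned effect. The expected 0.47 becomes 0.37 or 0.57, depending on direction.
- δ = 0.2 SD: 0.2 / 0.47 = 43%. The expected 0.47 becomes 0.27 or 0.67.
- If the contrast is instead adjusted for baseline with slope 0.5 (assumed), the movement halves to 0.05–0.10 SD: 0.05 / 0.47 = 11% and 0.10 / 0.47 = 21%.
- If the shift persists unchanged to post-treatment, it cancels in the change contrast.

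With no true effect and 72 per arm, the chance of a significant result in the direction of the shift is Φ(δ√(72/2) − 1.96) = Φ(6δ − 1.96). This is Φ(−1.36) = 0.087 at δ = 0.1 and Φ(−0.76) = 0.224 at δ = 0.2, against a nominal 0.025. The calculation takes the SD of the change as equal to the SD in which g is expressed. Since the variance of change is 2(1 − ρ), this holds when the pre–post correlation ρ is 0.5.

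**4. Effect of losing baseline non-completers (assumed rates).** The article gives no rate. Start from 80 per arm, apply the planned 10% attrition, then a further loss b: n = 80 × 0.9 × (1 − b), and power = Φ(0.47√(n/2) − 1.96).

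| b | n per arm | Power |
|---|---|---|
| 0 | 72.0 | 0.805 |
| 5% | 68.4 | 0.785 |
| 10% | 64.8 | 0.763 |
| 15% | 61.2 | 0.739 |
| 20% | 57.6 | 0.713 |

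This applies only if those people are left out of the analysis and are not already counted within the 10%.

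**The case against.** The strongest reply is that the order is inferred. The Randomisation section does not say that nothing comes between the interview and the envelope, and the flow chart that might settle it is not shown. Table 1's Pre-treatment column also holds the MINI and DES, which must precede allocation because they decide eligibility. Its footnotes re-time the mid- and post-treatment columns for the waitlist but not the Pre-treatment column. A PCL-C before allocation in both arms is therefore possible. This reply stands for the iCBT arm. It does not remove the point for the waitlist, whose first assessment is placed in week 1 in two sections, and nothing names an earlier PCL-C as the analysis baseline.

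A reader might infer several stronger things that the article does not support:

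- *That every baseline measure is unblinded in both arms.* The MINI, DES and PHQ-9 item 9 come before the envelope. The CEQ is said only to be completed at baseline.
- *That people without a baseline are certainly lost, or that the withdrawal list proves the order.* The wording is that they may be withdrawn, which typically closes course access. That is not deletion from the analysis, and the list does not say whether these withdrawals come before or after the envelope.
- *That losses fall mostly on the iCBT side.* The waitlist has its own, more firmly worded condition for remaining in the trial. Participants and recruitment also omits the data of waitlist participants who start outside trauma-focused treatment. The net direction is unknown.
- *That the bias has been measured.* The 0.1–0.2 SD shift has no source in the article.
- *That the moderator analyses are compromised.* The examples given, time since trauma and number of events, are historical facts that allocation would not obviously alter.

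**Conclusion.** The point holds in limited form. As written, allocation may be opened before the baseline PCL-C, IUS-12 and ERQ. In the waitlist arm the first listed assessment does follow allocation in unblinded participants. In the iCBT arm this is probable but not certain. Separately, the conditions for withdrawal and for remaining in the trial differ by arm and do not fit the intent-to-treat label, because the article does not say that people so removed stay in the analysis.

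The size and direction of any bias are unknown. The 21–43% of g = 0.47 rests on an assumed baseline shift of 0.1–0.2 SD in one arm that does not persist to post-treatment. The fall in power from 0.805 to between 0.785 and 0.713 rests on an assumed 5–20% loss beyond the planned attrition. The sample size of 72 per arm is unaffected. The change is worth making because it is cheap and removes the question.

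**What to change.** 1. In Randomisation, for participants not yet randomised, state that the envelope is opened only after electronic consent and completion of the baseline PCL-C, IUS-12 and ERQ. Use those values as the baseline in both arms, and align the Abstract, Table 1 and Participant monitoring with this.
2. In Statistical methods, state that every randomised participant stays in the intent-to-treat set whatever their baseline completion, program commencement or later questionnaire completion. The right to ask for one's data to be excluded, already given in Participants and recruitment, remains. Report baseline non-completion by arm.
3. Word the second change as a rule for the analysis set only. Decisions on course access are not affected.

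**Cost.** An existing online step is moved earlier, and a few applicants are lost before randomisation instead of after it. The trial had already begun: Trial status reports 26 participants meeting eligibility at submission, against a minimum of 2 × 72 = 144. Those already enrolled will have the earlier baseline order, so the report should state the change and how many participants fall under each order.

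If a PCL-C before allocation already exists in both arms, saying so and naming it as the baseline would meet the first item for the PCL-C. The IUS-12 and ERQ would need the same statement.

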### Primary outcome measures

Administration time points for all instruments are contained in Table 1.

**Table 1 Tab1:** Administration time points for questionnaires used in the RCT

	Administration time point				
Measure	Pre-treatment	Before each lesson	Mid -treatment^d^	Post-treatment^e^	3-month follow-up^f^
LEC^a^	♦				
DES	♦				
MINI	♦				♦
PCL-C^b^	♦	♦	♦	♦	♦
BDI-II^c^	♦		♦	♦	♦
PHQ-9	♦		♦	♦	♦
K10	♦	♦	♦	♦	♦
GAD-7	♦		♦	♦	♦
CEQ	♦			♦	
IUS-12	♦		♦	♦	♦
ERQ	♦		♦	♦	♦
SUDOR	♦		♦	♦	♦
SAPAS	♦				

*LEC* Life Events Checklist, *DES* Dissociative Experiences Scale, *MINI* Mini International Psychiatric Interview, *PCL-C* PTSD Checklist **–** Civilian version, *BDI-II* Beck Depression Inventory – Second Edition, *PHQ-9* Patient Health Questionnaire 9-item version, *K10* Kessler Psychological Distress Scale 10-item version, *GAD-7* Generalised Anxiety Disorder 7-Item Scale, *CEQ* - Credibility and Expectancy/Satisfaction Questionnaire, *IUS-12* Intolerance of Uncertainty Scale 12-item version, *ERQ* Emotion Regulation Questionnaire, *SUDOR* Service Utilisation and Days Out of Role Questionnaire, *SAPAS* Standardised Assessment of Personality - Abbreviated Scale

^a^Refers to both LEC-IV and part 2 of LEC-5

^b^Includes items 10, 11, and 16 from PCL-5

^c^Item 9 only

^d^Waitlist control group completes these measures at week 5 of the waitlist period

^e^Waitlist control group completes these measures at week 11 of the waitlist period

^f^Treatment group only

**Posttraumatic stress disorder Checklist – Civilian version** (PCL-C) [40]. The PCL-C is a 17-item self-report questionnaire providing a continuous measure of PTSD symptomatology, conforming to Diagnostic and Statistical Manual of Mental Disorders, Fourth Edition (DSM-IV) diagnostic criteria. Each item reflects a PTSD symptom and is rated on a 5-point scale for distress (1 = “Not at all”; 5 = “Extremely”). Items 10, 11 and 16 from the PCL-5 [41] will also be administered, which assess new diagnostic criteria for PTSD in the fifth edition of the DSM [DSM-5 1]. This approach was adopted in favour of sole use of the PCL-5, which had not been validated at the time of trial design. This will enable examination of change in the new PTSD symptoms in DSM-5.

**PTSD diagnostic status**. Change in PTSD diagnostic status will be indexed using the MINI PTSD module. The MINI has sound reliability and validity psychometrics [39].

### Secondary outcome measures

**Patient Health Questionnaire 9-item scale** (PHQ-9) [42]. The PHQ-9 is a self-report questionnaire corresponding to DSM-IV diagnostic criteria for major depressive disorder. Each item is rated in frequency on a 4-point scale (0 = “Not at all”; 3 = “Nearly every day”). Total scores range from 0 to 27 with higher scores reflecting greater symptom severity. The PHQ9 demonstrates sound psychometric properties and has been used extensively to measure treatment outcomes during internet CBT interventions targeting depression and anxiety [43, 44].

**Kessler-10 Psychological Distress Scale** (K10) [45]. The K10 consists of 10 items ranked on a 5-point scale designed to measure non-specific psychological distress. For the current study, the time frame was modified to assess psychological distress in the past 2 weeks rather than in the past 30 days. The K10 possesses strong psychometric properties [45, 46].

**Generalised Anxiety Disorder 7-Item Scale** (GAD-7) [47]. The GAD-7 is composed of seven items examining GAD symptom severity and is based on DSM-IV criteria. Items are measured on a 4-point scale for frequency of interference from symptoms over the past 2 weeks (0 = “Not at all”; 3 = “Nearly every day”). Internal consistency and test-retest reliability are high [47, 48].

**Intolerance of Uncertainty Scale – Short Form** (IUS-12) [49]. The IUS-12 is a psychometrically reliable, valid measure of intolerance of uncertainty [49]. It contains 12 items, each measured on a 5-point scale from 1 (“Not at all characteristic of me”) to 5 (“Entirely characteristic of me”).

**Emotion Regulation Questionnaire** (ERQ) [50]. The ERQ is a 10-item self-report measure of cognitive reappraisal and emotional suppression as means of regulating emotion. Items are scored on a 7-point scale to represent their use by the individual from 1 (“Strongly disagree”) to 7 (“Strongly agree”). This measure has sound reliability (including test-retest reliability) [51].

**Service Use and Days Out of Role Questionnaire - modified** (SUDOR) [52]. The SUDOR contains three items that measure the impact of symptoms on daily functioning including doctor (or other health professional) visits and days out of role or reduced functioning due to symptom impact. Items are presented in the form of open questions. Four additional items were included enquiring as to medication use and additional current treatment or activities undertaken to manage symptoms.

**Credibility and Expectancy/Satisfaction Questionnaire** (CEQ) adapted from [53]. At baseline, participants will complete two treatment expectancy questions: (1) “At this point, how logical does the program offered to you seem?” (0 = “Not at all logical”; 9 = “Very logical”) and (2) “At this point, how successfully do you think this treatment will be in reducing your PTSD symptoms?” (0 = “Not at all useful”; 4 = “Very useful”). Following the combined intervention, participants will also rate treatment satisfaction: “How satisfied are you with the skills that this program has taught you to manage your PTSD?” (1 = “Not at all satisfied”; 9 = “Very satisfied”); “How confident would you be in recommending this treatment to a friend who experiences similar problems?” (1 = “Not at all confident”; 9 = “Very confident”); followed by two questions about difficulty with the program and requesting additional feedback, which will require free text responses.

### Additional measures

**Life Events Checklist for DSM-IV** (LEC-IV) [54]. The LEC-IV will be used to screen for exposure to traumatic life events. The LEC-IV assesses exposure to 16 potentially traumatic events (PTEs) plus one “other” item to capture PTEs not included in other items. It requires respondents to code how each event was experienced (i.e. “It happened to me; I witnessed it; I learned about it; Not sure; Doesn’t apply to me”). It has sound test-retest reliability and convergent validity with comparable measures [55].

**Part 2 of the Life Events Checklist for DSM-5** (LEC-5) [56]. The LEC-5 will be used to obtain additional information about reported traumatic life events not obtained from LEC-IV, including brief description of event, time since trauma, traumatic event frequency.

**Beck Depression Inventory – Second Edition – Question 9** (BDI-II) [57]. The BDI-II is a 21-item self-report inventory that measures depressive symptoms. The BDI-II possesses high internal consistency, with alpha coefficients of 0.86 and 0.81 for psychiatric and non-psychiatric populations, respectively [57]. Only Question 9 from this questionnaire will be used to help determine suicidal ideation and suicide risk. Patients indicate their level of intent to commit suicide, on a 4-point scale (0 = “I don’t have any thoughts of killing myself”; 3 = “I would kill myself if I had the chance”).

**Dissociative Experiences Scale** (DES) [58]. This is a 28-item measure of dissociative symptoms. Respondents indicate the frequency of dissociative experiences on an 11-point scale, increasing in 10-point increments from 0 % (never) to 100 % (always). This measure has strong internal consistency and reliability over time [59].

**Skills of Cognitive Behaviour Therapy for PTSD Questionnaire**. This measure has been adapted from the Skills of Cognitive Therapy – Patient version [60]. It is a 20-item self-report measure designed to assess patients' understanding and use of basic CBT skills in the PTSD program. Ratings of patients' skill usage are made on a 5-point scale (1 = “Never”; to 5 = “Always or when needed”). Higher scores reflect greater patient subjective skill in applying CBT therapy principles for their PTSD.

**Likely Comorbid Diagnostic Status**. Likely comorbid generalised anxiety disorder (GAD), social phobia (SP), panic disorder, agoraphobia and obsessive compulsive disorder (OCD) status will be indexed by asking the initial enquiry question from the relevant module in the MINI.

**Standardised Assessment of Personality** – **Abbreviated Scale** (SAPAS) [61]. The SAPAS is an 8-item screen for DSM-IV personality disorder, with each item requiring a Yes/No response. It is a sensitive, specific measure of likely personality disorder [61].

